#### Potential confounders/modifiers

- Demographics patient and caregiver (age, sex, SES)
- Family relation patient-caregiver
- Duration and hours of caregiving
- Type of caregiving (instrumental, 24 hours supervision, travel)
- Social support of caregiver with a Social Support Assessment based on the Caregiver Assessment Battery used in the studies of Mittelman (Mittelman 2006).
- Loneliness with the Jong-Gierveld loneliness scale (de Jong-Gierveld 1985)
- (Instrumental) Activities of daily living of the patient (Lawton 1969; Katz 1963)
- Type of dementia
- Cognition of patients with the Mini Mental Status Examination (MMSE, Folstein 1975)
- Behavioural symptoms: Neuropsychiatric Inventory (NPI) (Cummings 1998)
- Medical co-morbidity and treatment (e.g. anti-depressants, benzodiazepines, anti-Alzheimer drugs, dementia type)

- Formal care support (e.g. respite care, meeting centre, elderly welfare advisor, Alzheimer café, home nursing)

## **6.2 Informed consent**

Written informed consent from both patient and caregiver is obtained. In case of mental incompetence of a patient the legal representative will sign the consent for the patient. If there is no legal representative or curator the family caregiver will sign the consent for the patient (only spouses, children (-in-law) and brothers/sisters of the patient). We will emphasize that the intervention focuses mainly on the informal caregiver. The dementia patient will always receive the care he or she needs and the family meetings will be an extra service to support the primary caregiver. The data of the patient are obtained to measure whether the patients quality of live improves if his/her informal caregiver gets more support. The data of the patient is also needed to correct for potential confounders and modifiers.

## **6.3 Study procedures**

After informed consent both patient and primary caregiver have to fill in several questionnaires (patients will be interviewed depending on their capabilities). The measurements at baseline and follow up (at 6, 12, 18 and 24 months after baseline) are done by independent and blinded assessors.

## **6.4 Randomisation, blinding and treatment allocation**

Pairs are randomized after baseline measurement. We will be able to detect and monitor selection bias as eligibility of caregivers will be routinely tested during the diagnostic work up. Baseline and follow up data are gathered by independent and blinded interviewers. After randomisation, participants included in the intervention will follow the different stages (described in paragraph 5.2)

## **6.5 Statistical Analysis**

Intervention effects will be analysed with survival analysis (Cox Proportional Models) for the time to incident affective disorder and repeated measurement analyses for number of symptoms. Both techniques can adjust for possible baseline imbalance, and potential modifiers (e.g. gender caregiver, relation with patient, patient centre). Dropout and loss to follow up will be described.

## **6.6 Withdrawal of individual subjects**

Subjects can leave the study at any time for any reason if they wish to do so without any consequences. The investigator can decide to withdraw a subject from the study for urgent medical reasons.

### **Follow-up of subjects withdrawn from treatment**

Data will be primarily analysed according to the Intention to treat principle, i.e. including all participants with valid data, regardless of whether they did or did not receive the intervention. Subsequently, the results of the intention to treat analysis will be compared with the results of the 'on treatment' analysis, to assess whether protocol violations have caused bias. Participants with documented deviations from the protocol (i.e. participants who did not receive the entire intervention or participants in either the intervention or the control group with incomplete

follow-up data) will be excluded from the on treatment analysis. Comparability between the intervention and usual care groups will be assessed at baseline to check differences.

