## 3 STUDY DESIGN

### 3.1 Design

Randomised controlled indicated prevention trial.

After selection and baseline assessment, study subjects are randomised to one of two groups; the intervention group receives usual care plus family meetings, the control group receives usual care only. Participants are free to seek additional assistance and support elsewhere at any time throughout 24 months follow-up. The study subjects are recruited through several memory clinics and specialized mental health care institutions.

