## **5 INTERVENTION**

### **5.1 Description**

The purpose of family counseling is to help family members provide emotional and instrumental support to the primary caregiver, the family member who carries the greatest weight of the caregiving, and to help all family members adapt to the changes that the demented process imposes on them.

The four family counseling sessions will follow the manual (Mittelman 2003). Four family meetings are scheduled within 8 months and run by a counselor with an advanced degree in nursing, social work or allied professions. Counselors receive a training based on the manual and train their skills prior to the study. One counselor is assigned to one caregiver to establish an ongoing relationship with someone who is familiar with the situation. The aims of the family meetings are: 1) to educate families about dementia consequences and resource information for care support; 2) to mobilize naturally existing family networks of patient and primary caregiver in order to improve emotional and instrumental support; 3) to teach problem solving and techniques for troublesome patient behavior that can be used after family counseling ends. The content of the sessions is also determined by the needs of each caregiver. For example, learning techniques, for management of troublesome behavior, promoting communication between family members. All sessions are audio-taped for supervision, intervision and detailed analysis.

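### The on-treatment set is selected after randomisation and can be biased in either direction, so its difference from the intention-to-treat result cannot show that protocol violations caused bias

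*Protocol*

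**What the plan says.** All references are to the Protocol.

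- **Primary analysis** (6.6, Follow-up of subjects withdrawn from treatment): "Data will be primarily analysed according to the Intention to treat principle, i.e. including all participants with valid data". The sentence goes on to say that this holds whether or not the intervention was received.
- **Secondary analysis** (same place): the ITT results are "compared with the results of the 'on treatment' analysis, to assess whether protocol violations have caused bias".
- **Who is removed** (same place): "participants who did not receive the entire intervention or participants in either the intervention or the control group with incomplete" records after baseline. Both kinds of participant are left out of the secondary analysis.
- **Arms** (3.1): "the intervention group receives usual care plus family meetings, the control group receives usual care only".
- **Length of the intervention** (5.1): "Four family meetings are scheduled within 8 months".
- **Outcome and model** (6.3, 6.5): time to incident affective disorder in a Cox model, with assessments at 6, 12, 18 and 24 months after baseline.

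**The concern.** The two exclusions act differently, and neither yields a set that can serve as a yardstick for ITT.

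**Non-completion.** A control caregiver has no meetings to miss, so this exclusion can act only on the intervention arm. Whether all four meetings were received is settled after randomisation, in a window that contains the 6-month assessment. An intervention caregiver who becomes a case and then stops attending is removed together with the event. The comparable control caregiver stays in.

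**Incomplete follow-up.** This applies to both arms, so it is not one-sided. It discards caregivers whom a Cox model can keep up to the time of censoring, provided censoring is unrelated to risk. The protocol does not say whether a caregiver who has an event and then misses later visits counts as incomplete. On a literal reading that event is lost too.

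The plan then uses this selected set "to assess whether protocol violations have caused bias". That is the wrong way round: the set without the protection of randomisation is used to judge the one that has it. At stake is how a discrepancy is read. With a null ITT result and a favourable on-treatment result, the stated purpose of the comparison invites the explanation that violations had distorted ITT, when the exclusions alone could have produced the gap.

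**Working it through.** **Inputs from the documents.** Yearly incidence 30%, 73 per group, 15% loss, 172 pairs (4.4). Four meetings within 8 months (5.1). Visits every 6 months to month 24 (6.3). The protocol gives no figure for the on-treatment analysis, no expected completion rate, and no risk for non-completers. Those are assumed below and shown as ranges.

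**The plan's own figures.** A two-sided comparison of 30% with 10% at alpha 0.05 and 80% power, with continuity correction, needs 72 per group, against 73 stated. 2 × 73 × 100/85 = 171.8, i.e. 172. Both reproduce, so 30% is used as the incidence.

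**Step 1: events before the meetings need be finished.** Constant hazard λ = −ln(0.7) = 0.3567 per year, the same in both arms (no true effect), with month 8 counted from baseline.
- P(event before month 8) = 1 − 0.7^(2/3) = 0.2116, about 21%.
- P(event before month 24) = 1 − 0.7² = 0.51.
- Mean follow-up to event or month 24 = 0.51/0.3567 = 1.4299 years.
- Contribution to that mean from early cases = [1 − 0.7884 × (1 + 0.2378)]/0.3567 = 0.0678 years, where 0.2378 = λ × 2/3 and 0.7884 = 0.7^(2/3).

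**Step 2: remove a share q of the early cases from the intervention arm only.**
Event rate = (0.51 − 0.2116q)/(1.4299 − 0.0678q). Divide by 0.3567, the control rate.

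| q (assumed) | events | person-years | rate | ratio |
|---|---|---|---|---|
| 0.25 | 0.4571 | 1.4130 | 0.3235 | 0.91 |
| 0.50 | 0.4042 | 1.3960 | 0.2895 | 0.81 |
| 0.75 | 0.3513 | 1.3790 | 0.2547 | 0.71 |

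**Step 3: let caregivers without an early event also miss meetings, share r.**
Rate = [0.2116(1−q) + 0.2984(1−r)]/[0.0678(1−q) + 1.3621(1−r)], with 0.2984 = 0.51 − 0.2116 and 1.3621 = 1.4299 − 0.0678.
- q = 0.25: ratio 0.91 at r = 0; 0.94 at r = 0.10; 1.00 at r = 0.25; 1.18 at r = 0.50.
- q = 0.50: ratio 0.81 at r = 0; 0.88 at r = 0.25; 1.00 at r = 0.50.

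So for each q the Step 2 ratios are the extreme towards benefit. If the meetings end by month 6, early cases are 1 − 0.7^0.5 = 16% and the r = 0 ratios become 0.93, 0.85 and 0.78.

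**Step 4: simulated trials with no true effect.** 86 per arm, the protocol's visit times, 15% loss unrelated to risk, 2,000 trials per scenario, log-rank hazard ratio. Here non-completers are a type of caregiver with a persistently different hazard, equally common in both arms but excluded only from the intervention arm. Shares of 20%, 30% and 40% are assumed.

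| Hazard of non-completers relative to completers | On-treatment HR | False benefit | False harm |
|---|---|---|---|
| 0.5 | 1.15 / 1.23 / 1.34 | at most 1% | 8 / 12 / 17% |
| 1 | 1.00 / 1.00 / 1.01 | 2–3% | 2–3% |
| 2 | 0.85 / 0.79 / 0.73 | 9 / 13 / 18% | at most 1% |
| 3 | 0.78 / 0.67 / 0.61 | 15 / 29 / 37% | at most 0.2% |

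ITT on the same trials gave 0.99 to 1.01, with about 2–3% false findings in each direction. A separate scenario, in which half of the cases arising before month 8 stop attending, gave an on-treatment HR of 0.79 with about 14% false benefit. That is close to the 0.81 of Step 2.

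**Step 5: incomplete follow-up.** At the protocol's 15%, this exclusion removes 0.15 × 172 = 25.8, about 26 pairs. Some may also be non-completers, so this is an upper figure for the additional loss.

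**The case against.** ITT is primary and the on-treatment analysis is a customary secondary look, so the main conclusion does not depend on it. That stands, and it limits the importance of the point.

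Nothing in the protocol says that caregivers who develop a disorder stop attending. Session content follows the caregiver's needs (5.1) and ad hoc counselling can be added (5.2), so distressed caregivers might be more likely to stay. A caregiver can also become a case, complete all four meetings and be retained, so calling this immortal time would be inexact; it is possible selection through attrition. This also stands.

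Two stronger readings are tempting and should be resisted.

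- A reader might infer that the analysis would show a benefit when there is none. The documents do not support that certainty. They give neither completion rates nor the risk of non-completers, and the null result ranges from apparent benefit through no bias to apparent harm. Even the worst scenario above gives a significant false benefit in about 37% of trials.
- A reader might infer that the plan has a rule by which a favourable on-treatment result means a real effect was diluted. Section 6.6 has no such rule and names no direction. It says only that the comparison assesses whether violations caused bias.

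The restriction of ITT to participants "including all participants with valid data" is a minor matter. The rest of that sentence keeps people regardless of treatment received, and exact set definitions may sit in a SAP that is not at hand.

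None of this rescues the bias check. A comparison that can err in either direction, by an amount nobody can state beforehand, cannot diagnose bias in ITT. Section 6.6 itself fixes both the exclusion rule and the use made of it, so this is not detail left to a SAP.

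**Conclusion.** The point holds for the on-treatment analysis and the inference drawn from it. The non-completion exclusion acts on one arm only and is decided after randomisation. The follow-up exclusion discards usable data in both arms.

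With no true effect and 30% yearly incidence, the event-rate ratio is about 0.91, 0.81 or 0.71 if 25%, 50% or 75% of cases before month 8 stop attending and nobody else does. Those are limits under that mechanism. The ratio is about 1.0 if completion is unrelated to risk, and above 1 if non-completers are at lower risk. Over the assumed scenarios with non-completers at persistently different risk, the on-treatment hazard ratio runs from 0.61 to 1.34 while ITT stays at about 1.00. A lean towards benefit is plausible if distressed caregivers stop attending, but the documents do not establish it.

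The wording should be changed. The primary result is not threatened.

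**What to change.** In section 6.6:

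1. Delete the statement that comparing ITT with on-treatment assesses bias from protocol violations.
2. Define ITT as all randomised pairs, each contributing follow-up to event or censoring.
3. Do not exclude anyone for incomplete follow-up; censor at the last assessment and keep any event recorded before dropout.
4. Label any on-treatment analysis exploratory, and state that it is a non-randomised comparison.

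These are wording changes, cost almost nothing and leave the design untouched.

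Optionally, replace the on-treatment analysis with a complier-average estimate that uses randomisation as the instrument, with a completion threshold defined in advance and all controls retained. This costs more: a wider interval, the assumption that allocation affects the outcome only through the meetings, and additional modelling work because the outcome is a time to event. It is not needed to resolve the point.

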## **7 SAFETY REPORTING**

### **7.1 Section 10 WMO event**

In accordance to section 10, subsection 1, of the WMO, the investigator will inform the participants and the METC-VUmc if anything occurs, on the basis of which it appears that the disadvantages of participation may be significantly greater than was foreseen in the research proposal. The study will be suspended pending further review by the METC-VUmc, except insofar as suspension would jeopardise the subjects' health. The investigator will take care that all subjects are kept informed.

### **7.2 Adverse and serious adverse events**

It is very unlikely that the intervention will cause serious adverse events as it concerns a psychosocial intervention. This was demonstrated in earlier studies which organized family meetings in a similar way (Mittelman 2003). The only imaginable side-effect may be that the patient is confronted in a more intensive way with the nature of his or her mental condition. However, this may also be the reason why this intervention works. The pilot which the VUmc site already started has given positive reactions from the participating families as well. When serious adverse events will appear, it will be reported to the METC-VUmc according to the requirements of that METC.

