### Nature and extent of the burden and risks associated with participation, benefit and group relatedness

The burden of the intervention will be minimal for the dementia patients and their family caregivers. A possible burden can be created by the number of questionnaires which will be taken to assess the study parameters. Furthermore, emotional discomfort and family conflicts can exist as a consequence of participation in the intervention. This possible burden will be in proportion to the potential value of the research.

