#### ***Follow up***

Review of the previous session, previous commitments, task assignments, discussion of progress of carrying out tasks, identifying issues for current consideration. During the session it will become clear that some issues are resolved while others have taken a higher priority. In addition, new issues, problems, and conflicts will emerge. These are discussed in the same way as the original issues were in the first session. The counsellor concludes by discussing the date and time of the next session and who will attend. If the next meeting will be the last family session, the family should be reminded of that fact so that it does not come as a surprise and the can prepare for termination.

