#### **Follow-up of adverse events**

All adverse events will be followed until they have abated, or until a stable situation has been reached. Depending on the event, follow up may require additional tests or medical procedures as indicated, and/or referral to the general physician or a medical specialist.

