### **8.4 Benefits and risks assessment, group relatedness**

The primary informal caregiver will be interviewed to assess the incidence of anxiety and depressive disorders in the study population. Patients will be interviewed to measure their quality of life and cognitive functioning. Emotions and conflicts between family members of the dementia patient can be a possible discomfort as a consequence of the participation in family meetings. In our opinion, this possible burden will be in proportion to the potential value of the research. There are many indications that this is generally a (cost)effective approach to prevention although it has not yet been studied for this specific group (Beekman ATF, Cuijpers P, van Marwijk HWJ, et al, Prevention of psychiatric disorders [In Dutch: Preventie van psychiatrische stoornissen.]. Ned Tijdschr Geneesk 2006;150:419-23.). We have started to pilot the intervention with two families (VUmc), and the first reactions were very positive. As demonstrated in the landmark studies of Mittelman et al., family meetings, designed to mobilize support of naturally existing family networks, appear to be among the most powerful psychosocial interventions to reduce depression in caregivers (Whitlatch 1991, Mittelman 1995, 1996, 2004).

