### **8.5 Compensation for injury**

We obtained dispensation from the statutory obligation to provide insurance, because participating in the study is without risks for informal caregivers and patients.

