### **9.3 Annual progress report**

The investigator will submit a summary of the progress of the trial to the accredited METC once a year. Information will be provided on the date of inclusion of the first subject, numbers of subjects included and numbers of subjects that have completed the trial, serious adverse events/ serious adverse reactions, other problems, and amendments.

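### Sections 7.2 and 8.5 deny harms that the Summary and 8.4 say can occur, so the 7.1 trigger has no single baseline, and family conflict has no stated means of capture

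*Protocol*

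**What the plan says.** The Protocol describes the foreseeable harm of the family meetings in four places.

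- Section 7.2, in a paragraph arguing that serious events are unlikely: "The only imaginable side-effect may be that the patient is confronted in a more intensive way" with the nature of the illness.
- Section 8.5, as the reason why the insurance obligation was waived: "participating in the study is without risks for informal caregivers and patients".
- The Summary, under burden and risks: "emotional discomfort and family conflicts can exist as a consequence of participation in the intervention".
- Section 8.4: "Emotions and conflicts between family members of the dementia patient can be a possible discomfort as a consequence of the participation in family meetings".

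The Summary and 8.4 both judge this burden proportionate to the value of the research.

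On handling, 7.2 states: "When serious adverse events will appear, it will be reported to the METC-VUmc according to the requirements of that METC". The paragraph on follow-up of adverse events adds: "All adverse events will be followed until they have abated, or until a stable situation has been reached". The annual report in 9.3 covers "serious adverse events/ serious adverse reactions, other problems, and amendments". Section 7.1 requires participants and the METC to be informed, and the study suspended pending review, if the drawbacks of taking part may prove significantly worse than the proposal anticipated.

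**The concern.** A safety section that calls one effect the only conceivable one excludes every other effect, including those the same document discloses elsewhere. The effect it names falls on the patient. The Summary makes the caregiver the unit of analysis, and the meetings work through the caregiver's family, yet neither 7.2 nor 8.5 names a harm to caregiver or relatives.

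Two things are at stake. First, the METC receives inconsistent accounts of risk, and one of them is the stated ground for the insurance dispensation. Second, family conflict is the harm most closely tied to how the intervention works. If nothing ensures that it is collected, the trial may be unable to say whether the meetings raised or lowered it. Section 1.2 makes the harm plausible: it calls the family a possible source of stress and cites a survey in which three quarters of dementia caregivers reported conflict with relatives.

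**Working it through.** No arithmetic applies. The Protocol gives no rate of family conflict and no safety figure to reproduce, so the check is a comparison of sections.

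**Step 1: are the risk statements compatible?**

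| Section | Harm foreseen | Who is affected |
|---|---|---|
| 8.5 | None | Caregivers and patients |
| 7.2 | One effect, stated as exclusive | Patient |
| Summary | Emotional discomfort and family conflict, as possibilities | Not limited to one person |
| 8.4 | Emotions and conflict, as possibilities | Family members |

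The Summary and 8.4 agree with each other. Section 7.2 conflicts with both because its wording is exclusive. Section 8.5 conflicts with both because it denies any risk, and it also sits badly with the patient effect admitted in 7.2.

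**Step 2: does the conflict affect anything that operates in the trial?** Section 7.1 compares what happens with what was foreseen. The table offers three versions of that: nothing (8.5), one patient effect (7.2), or discomfort and family conflict (Summary and 8.4). The same run of family conflicts could be unforeseen under 7.2 and fully foreseen under 8.4. The trigger therefore lacks one consistent baseline.

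**Step 3: which of the disclosed harms would be captured?**

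- *Caregiver distress.* Section 6.1 makes disorder on the MINI and symptoms on the CES-D, GDS-5 and HADS anxiety scale main endpoints. Section 6.3 has them collected at 6, 12, 18 and 24 months by blinded assessors, and 6.5 analyses the intervention effect on disorder onset and symptoms. Worsening caused by the meetings would count against the intervention. This harm is measured and compared.
- *Caregiver burden.* The SSCQ and CRA are secondary endpoints in both arms.
- *Family conflict.* No endpoint in 6.1 is a measure of it. Social support and loneliness are listed, but as potential confounders or modifiers. The content of the social support instrument is not given, so whether it touches on conflict cannot be determined.
- *Distress in other relatives.* No measure is listed.

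**Step 4: does adverse event handling fill the gap?** The Protocol follows up all adverse events and reports other problems yearly. It does not define an adverse event or say how non-serious events are elicited. Follow-up begins only once an event has been recognised, so these provisions permit family conflict to be recorded but do not ensure it. Section 5.1 has every session audio-taped, for supervision and detailed analysis. The tapes are not described as a safety source and have no counterpart in the control arm.

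**The case against.** The strongest reply is that 7.2 forecasts side-effects and does not define adverse events. Nothing in it limits what staff may record. The follow-up paragraph covers every adverse event whatever its type or whoever it affects, 9.3 has a category for other problems, and 7.1 opens with a broad duty to inform. A reader might infer from 7.2 that conflict and distress would go unrecorded; the document does not say that. This part of the reply stands.

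A reader might also infer that the caregiver has no recognised harm, or that the trial would miss harm to caregivers because it does not look. Neither is supported. The Summary and 8.4 recognise the harm, and caregiver distress is a main outcome.

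Section 5.2 might be read as predicting harm, since it says of the follow-up meetings: "In addition, new issues, problems, and conflicts will emerge". In context this is material to be worked through in the session. It is not presented as a harm, and emotional discomfort is not mentioned. Likewise the Summary and 8.4 say these effects can happen, not that they are expected.

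On 8.5, it can be argued that a statement made for injury cover is compatible with disclosed discomfort, especially as 8.4 stands directly before it. That softens the conflict without removing it, because the sentence denies risk in general terms. Whether the dispensation depends on it is a legal question the document cannot answer.

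Finally, a table of events by arm could sit in a statistical analysis plan that is not shown. That is fair, but an analysis plan cannot tabulate what was never collected. How conflict is captured belongs in the Protocol.

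**Conclusion.** The point holds as a contradiction with a limited gap in data collection. Sections 7.2 and 8.5 cannot stand beside the Summary and 8.4, and until they are reconciled the 7.1 trigger has no consistent meaning. Two of the disclosed or closely related harms, family conflict and distress in relatives other than the caregiver, have no stated means of capture.

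No numerical size can be given. The Protocol offers no rate of conflict caused by the meetings, and assuming one would show only that some events are likely, not that any would be lost. The primary comparison is unaffected. The correction is worth making because it bears on participant safety and on what the METC is told, and because it is cheap. The conclusion assumes that no separate adverse event form or manual, outside the document reviewed, already asks about family conflict in both arms.

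**What to change.** 1. Rewrite 7.2 and 8.5 to agree with the Summary and 8.4. In 7.2, drop the exclusive wording and name family conflict and caregiver emotional distress as anticipated adverse events. In 8.5, delete the no-risk clause.
2. Submit the corrected risk statement to the METC, so that 7.1 refers to one account of what was foreseen.
3. Add one self-completed item on family conflict, identical in both arms, to the 6, 12, 18 and 24 month assessments, and report it by arm. Both arms are needed because background conflict is high by the Protocol's own account, so a count in the intervention arm alone could not be interpreted.
4. Keep the answers from the blinded interviewers. If an interviewer asked about conflict, the reply could reveal allocation and compromise later MINI assessments, even when the question follows the MINI at that visit. Caregivers already complete questionnaires, so this needs no new procedure.

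The cost is an amendment, one questionnaire item at existing assessments and one table. The insurance dispensation may have to be reconfirmed on the corrected statement.
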